## Abstract

**Introduction:**

Neurodevelopment and related mental disorders (NDDs) are one of the most frequent disabilities among young people. They have complex clinical phenotypes often associated with transnosographic dimensions, such as emotion dysregulation and executive dysfunction, that lead to adverse impacts in personal, social, academic, and occupational functioning. Strong overlap exists then across NDDs phenotypes that are challenging for diagnosis and therapeutic intervention. Recently, digital epidemiology uses the rapidly growing data streams from various devices to advance our understanding of health’s and disorders’ dynamics, both in individuals and the general population, once coupled with computational science. An alternative transdiagnostic approach using digital epidemiology may thus better help understanding brain functioning and hereby NDDs in the general population.

**Objective:**

The EPIDIA4Kids study aims to propose and evaluate in children, a new transdiagnostic approach for brain functioning examination, combining AI-based multimodality biometry and clinical e-assessments on an unmodified tablet. We will examine this digital epidemiology approach in an ecological context through data-driven methods to characterize cognition, emotion, and behavior, and ultimately the potential of transdiagnostic models of NDDs for children in real-life practice.

**Methods and analysis:**

The EPIDIA4Kids is an uncontrolled open-label study. 786 participants will be recruited and enrolled if eligible: they are (1) aged 7 to 12 years and (2) are French speaker/reader; (3) have no severe intellectual deficiencies. Legal representative and children will complete online demographic, psychosocial and health assessments. During the same visit, children will perform additionally a paper/pencil neuro-assessments followed by a 30-min gamified assessment on a touch-screen tablet. Multi-stream data including questionnaires, video, audio, digit-tracking, will be collected, and the resulting multimodality biometrics will be generated using machine- and deep-learning algorithms. The trial will start in March 2023 and is expected to end by December 2024.

**Discussion:**

We hypothesize that the biometrics and digital biomarkers will be capable of detecting early onset symptoms of neurodevelopment compared to paper-based screening while as or more accessible in real-life practice.

## Introduction

Neurodevelopmental and related mental disorders are one of the most frequent disabilities among young people. As stated by OCDE (2022), more than 166 million youth worldwide are affected by such conditions that are of significant concern in term of public health but also of economic burden (1) and social welfare (2).

Neurodevelopmental disorders (NDDs) are defined by the Diagnostic and Statistical Manual 5th Edition [DSM-5-TR (3) and in the International Classification of Diseases 11th version (ICD-11) (4)], as all structural or/and brain functioning anomalies that occur during a child development. They encompass intellectual handicaps (intellectual disabilities), attentional deficit/hyperactivity disorder (ADHD), communication disorders (language, speech, or communication deficits), specific learning disabilities (SLD, difficulty reading, or with written expression, or with numbers and mathematical reasoning etc.), developmental coordination disorder (DCD or dyspraxia), autism spectrum disorder (ASD). NDDs occur from early childhood and persist to adulthood for 50% (5). Negative impacts such as school dropout, loss of self-esteem or social interaction (6), severe neglect at home or bullying at school, can and do have enduring and damaging effects on the development of core cognitive and emotional skills, that are often lifelong conditions (1, 7).

The pathophysiology of NDDs is complex and remains largely unknown although multiple pre- and peri-natal environmental factors along with polygenic influences have been recognized (8–10). They are often associated with other somatic or psychiatric diagnoses (comorbid, concomitant or in continuum) (11–15). However, there are no psychological or biological consensual assessments, nor imaging techniques to make ascertain diagnosis of NDD, which today relies mainly on clinical evaluation. Furthermore, strong overlaps across NDD phenotypes make both group and distinction of each disorder difficult in real-life practice.

In addition to the clinical complexity, significant barriers prevent from NDDs and disclosing concerns. These include the stigma of mental health (16), lack of understanding of whether symptoms are abnormal or a typical experience, lack of time and lack of accurate trustable assessment tools (17), and knowledge of their interpretation, lack of referral processes and options, having providers or support persons underestimate their symptoms and concerns, and fear that reporting symptoms will lead others to think that parents or relatives are incompetent in their parenting or educating role (7, 18), leading to severely under detected and undertreated children with an estimated prevalence of NDDs quite high without standardized screening (19–21). Routine, standardized screening would significantly improve detection of neurodevelopmental alterations. However, the scarcity of human health resources poses a major deterrent to routine screening (7). E-screening has the potential to increase efficiency of mental healthcare by re-allocating limited human resources where they are most needed—in-depth follow-up assessment, referral, and treatment (22). It is a low-resource option that can be embedded in current routine practice across various settings and providers (for example, family physicians, child psychiatrists, psychologists, speech therapists, nurses) and thus will increase access to routine screening.

Importantly, e-screening through a careful gamification can address the most prominent barriers to screening identified by children, relatives, and healthcare providers. It would also ease the acceptability and feasibility in real life practice and provide personalization to patient needs (23) with real-time data (24–27) along anonymity (28–30). Recently, digital biomarkers have shown a strong potential to predict mental issues in adults (31–33), but none has investigated in children whether biometry could be relevant for a better understanding of neurodevelopmental conditions and for the identification potential subtypes as a NDD continuum in children (34). To our knowledge, no studies have evaluated e-screening based on multimodality biometry and digital biomarkers in children and in ecological context.

There is a clear need for a rigorous evaluation of the feasibility, acceptability, and psychometric performance of e-screening for large scale children and adolescent cohort. A key consideration for evaluation is to determine whether gamified e-screening delivered through an unmodified tablet are valid and reliable for use compared to well-established assessment tools. For example, it has been shown that some tools have different psychometric properties when delivered online, suggesting a need for different cutoff points (35).

Taken together, the need to identify screening and assessment tools that are acceptable to both children and health professionals, overcome barriers to accessibility-to-care, to implementation into routine care, and are cost-effective and clinically useful, is crucially needed.

Today, billions of people are increasingly generating and collecting health-related data online (36) or on mobile devices. The opportunities for more accurate and effective health services are enormous (37, 38). Digital epidemiology uses the new and rapidly expanding digital data streams from mobile devices to advance public and personalized health (39, 40). These datasets are then used by artificial intelligence algorithms to improve our understanding of health and disorders dynamics, both in individuals and in the general population. In natural environment, digital epidemiology represents a new approach that aims at measuring human behavior and may, combined with clinical (endo)phenotypes, enhance capability and sensitivity in early identification, diagnosis, and management of health conditions. Moreover, such a combined approach may easily allow clinicians to perform a more personalized and patient-tailored diagnostic and therapeutic approach.

As children and adolescents are so familiar with digital technologies (41, 42), building the right services specifically designed and dedicated to them will help to prevent, monitor, and intervene more appropriately on neurodevelopmental and related mental disorders at a larger scale.

Here, we investigate how digital phenotyping integrated with clinical (endo)phenotypes constitutes a new method for building comprehensive datasets based on digital epidemiology to create meaningful metrics of cognition, emotions, and behavior specific to children and adolescents. These detectable and measurable features will help understanding better brain development and hereby identifying prominent predictive variables to achieve dimensionality reduction and risk factors for NDDs.

**Purpose** (Table 1)—the EPIDAI4Kids study will examine brain functioning in children aged 7 to 12 years using biometrics and digital biomarkers to create meaningful metrics of cognition, emotions, and behavior specific to children and adolescents, while they are playing at gamified assessments on an unmodified tablet.

**Table 1 tab1:** Primary and secondary objectives, research questions, and hypotheses.

Primary objective	Research question	Outcome	Measures	Testable hypothesis
To create and compare a normative base of brain functioning in children aged 7 to 12 years using multimodality biometry e-measurements vs. paper-based screening	Is the neuro-developmental e-assessments as or more acceptable to children and health practitioners than paper-based screening?	Acceptability: % children in the study failing finishing the e-assessments	Acceptability	Higher proportion of children and health practitioners will affirmatively respond to acceptability for the e-measurement
		% of participants reporting that e-questions and psychometric games are easy to navigate around on the tablet	Qualitative; semi-structured interview	
			Quantitative: proportion of participants feeling uncomfortable	
To compare psychometric properties (sensitivity, specificity, cutoff points) of paper-based screening vs. the psychometric games?	What are the performances in cognition, emotion and/or behavior in children aged 7 to 12 years on child neurodevelopment?	Efficiency: correlations between scoring of paper-based screening performances and biometrics within each participant and inter-examinator	Quantitative: video and audio will be recorded for about 30 min while the children are playing on a unmodified tablet. Eye-, face- digit- and sound- will be extracted from recorded video by ML/DL algorithms.	Strong correlations between paper-based screening performances (psychometric properties) and multimodality biometrics within each participant.
				Less variability inter-examinator on e-assessments than on paper-based screening
Secondary objective	Research question	Outcome	Measures	Testable hypothesis
To compare feasibility of the multimodality biometry e-measurements?	Is the neuro-developmental e-assessments as or more feasible to children and health practitioners than paper-based screening?	Feasibility: % children in the study failing finishing the e-assessments	Qualitative: semi-structured interviews	Higher proportion of children and health practitioners will affirmatively respond to feasibility for the e-measurement
		% of health practitioners reporting that e-questionnaires and psychometric games are easy to navigate around on the tablet		
To validate the clinical relevance of multimodality biometrics	Are multimodal biometry e-measurements clinically relevant metrics for neurodevelopmental and mental health?	Match mobile EEG biomarkers for neurodevelopmental and mental health with multimodality biometrics	Quantitative: electroencephalographic (EEG) biomarkers of cognitive, emotional, and behavioral performance in children aged 7–12 years	Compare EEG signals obtained while children are playing with biometrics measurements related to well-characterized EEG signatures for related mental health in children (P2, N170, P300 amplitude and latence, Ratio Theta/Beta (TBR), Frontal Theta and Delta Power, Posterior Alpha et beta Power)
To determine factors associated with level of disclosure of symptoms related to neurodevelopmental and mental health	What factors are associated with risk of neurodevelopmental and mental health?	Identification of factors that significantly increase odds of neurodevelopmental and mental health reported symptoms	Quantitative: (1) demographic variables (age, gender, SES), (2) medical status (current NDD status, history), (3) psychopathological scores and quality of life (BRIEF, CBCL, ADHD scale, ASQ-10, PSQI, Grit questionnaire, SMQ)	Compared to paper-based screening, e-screening promotes greater disclosure
To determine multimodality biometric e-assessment as a monitoring tool		Examination of significant changes of either or both scores compared with baseline (repeated testing)	Quantitative: compared 4-month follow-up scores of e-assessment and paper-based screening with those obtained at baseline	More variability of scoring in those obtained from paper-based screening will be expected than those from e-assessment

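### Primary acceptability and secondary feasibility share the same first-listed outcome, non-completion by children, and that outcome does not match the affirmative-response hypothesis of either

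*Protocol article*

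**What the plan says.** All of this is in the protocol article, Introduction, Table 1.

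- **Acceptability (primary).** The research question is "Is the neuro-developmental e-assessments as or more acceptable to children and health practitioners than paper-based screening". The first outcome is "Acceptability: % children in the study failing finishing the e-assessments". The second is the percentage "of participants reporting that e-questions and psychometric games are easy to navigate around on the tablet". The Measures column adds "Quantitative: proportion of participants feeling uncomfortable". The testable hypothesis is "Higher proportion of children and health practitioners will affirmatively respond to acceptability for the e-measurement".
- **Feasibility (secondary).** The research question has the same form, with feasibility in place of acceptability and again with paper-based screening as the comparison. The first outcome is "Feasibility: % children in the study failing finishing the e-assessments". The second is the percentage "of health practitioners reporting that e-questionnaires and psychometric games are easy to navigate around on the tablet". The hypothesis is "Higher proportion of children and health practitioners will affirmatively respond to feasibility for the e-measurement".

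The sections Primary objective, Secondary objectives and Aims of the study name acceptability or feasibility in places, but give neither another definition.

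**The concern.** A primary and a secondary endpoint should each carry their own information, and each hypothesis should be stated on the quantity that will be measured for it. Here the first-listed outcome is the same in both rows, and it is not the quantity that either hypothesis speaks about.

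Non-completion is a count of failures among children. The hypotheses concern favourable answers from children and from practitioners. A child may enjoy the games and stop because time runs out or the tablet fails, and another may finish while uncomfortable. Two things are at stake. A favourable completion rate could be presented twice, as if feasibility confirmed acceptability. And the primary acceptability question could be answered with a figure that does not address its hypothesis.

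**Working it through.** The document gives no completion rate, affirmative-response rate or margin for either endpoint, so there is no figure of the plan to reproduce. The check sets the two rows of Table 1 side by side.

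| Element | Acceptability (primary) | Feasibility (secondary) | Same? |
|---|---|---|---|
| First outcome | % of children not finishing | % of children not finishing | Yes |
| Second outcome | Ease of navigation, rated by participants | Ease of navigation, rated by practitioners | Same property, different rater |
| Discomfort | Listed | Not listed | No |
| Quantity in the hypothesis | Affirmative responses, children and practitioners | Affirmative responses, children and practitioners | Same form |
| Comparator in the question | Paper-based screening | Paper-based screening | Yes |
| Paper-based value in an outcome line | None | None | Yes |

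**Step 1: duplication.** Let *x* be the number of children who do not finish and *n* the number assessed. The first acceptability outcome is *x/n*, and the first feasibility outcome is the same *x/n* in the same children. If both were tested, they would give the same p-value. Two independent tests at 0.05 without adjustment would have a joint error of 1 − 0.95² = 0.0975. Here it would stay at 0.05, because there is only one test. The second report adds no evidence. One of the two outcome lines in each row is affected.

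**Step 2: match to the hypothesis.** *x/n* is not a response, does not come from practitioners, and counts failure where the hypotheses predict a higher favourable proportion. No rule in the document converts finishing into an affirmative answer, so *x/n* does not determine the proportion that the hypotheses name.

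**Step 3: respondents.** Both hypotheses name children and practitioners. The Recruitment section describes participants as the child and the parent or legal representative. On that reading neither acceptability outcome line contains a practitioner statistic. Under feasibility, the only child statistic is the duplicated non-completion figure.

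**Step 4: comparator.** Both questions ask whether the e-assessment does as well as or better than paper-based screening, and both hypotheses predict a higher proportion. All four outcome lines describe the e-assessment alone, so as written none of them supplies the other side of the comparison.

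**The case against.** The strongest reply is that the endpoints are not the same. Each has a second outcome line with a different rater, and discomfort belongs to acceptability only. This stands. A reader might infer from the shared first line that feasibility merely repeats the primary endpoint. Table 1 does not support that; the repetition is confined to the first-listed component.

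A reader might also count non-completion, navigation, discomfort and affirmative response as four rival definitions of acceptability, and conclude that the false-positive rate is inflated or that the metric could be picked after the data are seen. The document does not support this either. Those items come from three different columns of the table, and the navigation item may be the response that the hypothesis has in mind. The Hypothesis testing framework section promises a multiplicity adjustment. A condensed article may also leave the interview items and the order of the components to the full protocol or analysis plan.

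Two further points are fair. Stopping early can reflect unwillingness as well as practical failure, so assigning completion to feasibility is a choice. And the reach is limited: the Sampling section does not base the sample size on acceptability, and the primary aim under Aims of the study does not mention it, although Primary objective does.

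None of this removes the core. Table 1 states both outcomes and both hypotheses, and they do not fit each other. This is a conflict in what is written, not detail left out, and an analysis plan that followed the table would inherit it.

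**Conclusion.** The point holds in limited form. The first-listed outcome is identical for a primary and a secondary endpoint and matches neither hypothesis. The endpoints differ only in who rates ease of navigation and in the discomfort measure. The acceptability outcomes omit practitioners, whom the hypothesis names, and no outcome line in either row gives a paper-based value.

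In size, this is one of two outcome lines in each row, and the duplicated figure is the same for every child assessed. No numerical error rate can be attached to it from the document. The conclusion rests on the wording of Table 1 and on reading participants as the Recruitment section does. It affects how the acceptability and feasibility results can be interpreted, not the sample size. It should be corrected because it concerns a primary outcome.

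**What to change.** Reword the two rows of Table 1.

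1. **Feasibility.** Use completion here only, as the proportion finishing the e-assessment among children who start it. State the feasibility hypothesis on completion, and bring the research question, which also names practitioners, into line.
2. **Acceptability.** Make the primary outcome the proportion responding affirmatively to one named item, reported separately for children and for health practitioners. Keep discomfort and ease of navigation as supportive measures, and remove non-completion from this row.
3. **Comparator.** State each hypothesis on its own outcome against the same quantity for the paper-based tests done at the same visit. If no paper-side rating is collected, restate the hypothesis as descriptive for the e-assessment alone. The section Questionnaires and neuro-assessments allows the WISC-V in digital or paper form, so the row should say which administration counts as the paper comparator.

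The cost is the rewording of two rows. Completion, ease of navigation and discomfort are already listed. The comparison may need one matching item or completion count on the paper side. If that cannot be added, the price is giving up the comparative claim for that endpoint.

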#### The multimodality biometry tool description

The XAI4Kids® Multimodality Biometry tool has been developed by O-Kidia, SAS, and is composed of several technological components (Tables 2
3):

▪ The unmodified tablet: data will be collected in ecological context during the session to minimize stigma. Participant’s main biometry parameters (e.g., eye-, face-, and digit-tracking, frequencies, etc.), clicking, taping, and video from the intrinsic camera will be recorded to reflect of the child’s performances.▪ The O-Games: a series of gamified psychometric sessions, which will engage the participants to perform as the best, and stimulate the cognitive, emotional, and behavioral functions of each participant. Games were developed for Android with Unity^1^ and will be installed on each participant’s table.

**Table 2 tab2:** Study workflow at baseline.

Name	Description	Time	Who	Visit
Screening worksheet	Eligibility criteria	10 min	Y, P	B
Modified Ohio State TBI Screen-Short Ver	TBI rule-outs at BL; TBI	5 min	P	B
Demographics domain	demographics, race, gender, family structure, SES	20 min	P	B
Medications	Medical history, medications	5 min	P	B
Pittsburgh Sleep Quality Index	Sleep habits	5 min	P	B, T2-end
Children’s Sleep Habits Questionnaire	Sleep habits	5 min	Y	B, T2-end
Questionnaires for parent	ADHD-rating scale, Children Behavior Check, BRIEF, DCDQ, Conners 3	20 min	P	B, T2-end
Questionnaires for child	ADHD-rating scale, ASQ-scale, Grit scale, and SMQ	20 min	Y	B, T2-end
WISC-V (substest)	7 subtests Symbol, Cubes, Code, Comprehension, Letter-Number sequences, matrix, and similitude	45 min	Y	B, T2-end
O-Games battery	5 psychometric games	20–35 min	Y	B, T2-end
Breaks	As much as needed	20 min	Y	B, T2-end

**Table 3 tab3:** Convergent validity measures for the XAI4Kids^®^ e-measurement tool.

What it measures	Stream data type	Convergent validity measures
Visio-spatial processing	Rocket	WISC-V, block design
	SES4ME	WISC-V, symbol search
	O-TOM	WISC-V, barrage
Working memory	Untangle, EEG (P3b)	WISC-V, letter-number sequences
Episodic memory	O-G	WISC-V, letter-number sequences, digit-span
Attention	Rocket, connect	WISC-V, digit span, coding, symbol search
Speed processing	Connect	WISC-V, symbol search (immediate recall) coding
Language	O-KIDO	WISC-V, comprehension, vocabulary,
Executive functions	O-MAZE	WISC-V, BRIEF, vocabulary,
Auditive Attention	O-METRO	WISC-V, digit span
Anxiety	EEG and video-analysis	CBCL subtest
Sleep	EEG and video-analysis	PSQI

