Motivation	EEG and video-analysis	SMQ, grit scale
Emotional control	EEG and video-analysis	BRIEF
Social abilities	O-TOM, EEG, and video-analysis	CBCL subtest, ASQ
Visual motricity	Eye-tracking	WISC-V, symbol search, coding
Visual acuity	Eye-tracking	WISC-V, symbol search

In addition, the tool is constituted by:

▪ The AI module: the backend part of XAI4Kids® system will allow the clinical recommendations of biometry extracted features (43–48) based on machine and deep learning algorithms. Data-driven coefficients from first-level analyses for each participant will be provided for each analysis. To facilitate Big Data deployment, and re-use, the computational workflows will be implemented as virtual machines (VMs), deployable on multiple computing resource and on local workstations. Each metric will be obtained from time-series data and stored in the time-series analysis database. The query object graph analysis method will be used to enable analysis sharing among analysts by preventing duplicate processing and data explosion (49).▪ The artificial setting: to extract features of interest from the signals, tracking software and algorithms have been specially developed for feature extractions.

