### Participant

The inclusion criteria will be: (i) boys or girls of any ethnicity, aged 7–12 years (typically developing and diagnosed with NDDs); (ii) French native speakers; (iii) normal hearings, normal or corrected-normal vision; (iv) no brain trauma; (v) an estimated intelligence quotient of 85 and above (exclusion if score < 25th percentile) based on Weschler’s subtests Matrix Reasoning and Similarities (50); (vi) no history of co-morbid psychiatric illness that might confound the analysis of the study (e.g., schizophrenia, obsessive-compulsive disorder, major depression, or bipolar disorder); (vii) ADHD medications and Selective serotonin reuptake inhibitors (SSRIs) are not exclusionary since use of these medications is associated with neurodevelopmental disorder condition, but the treatment will be suspended 2 days before any cognitive evaluation.

The exclusion criteria will be: (i) failure to meet the inclusion criteria; (ii) lack of written informed consent: the child and at least one of the parents (or the legal representative) must sign the informed consent form.

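### Table 3 pairs visual acuity and episodic memory with subtests it uses for other domains, and two pairs of domains share both data stream and comparator, so a strong correlation there would not validate the named domain

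*Protocol article*

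**What the plan says.** In the protocol article, the primary-objective part of Table 1 gives the hypothesis as "Strong correlations between paper-based screening performances (psychometric properties) and multimodality biometrics within each participant". It states no numerical threshold. The Primary objective section says that the tool will be compared with current convergent validity measures, and Table 3, titled "Convergent validity measures for the XAI4Kids", lists them by domain and data stream.

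The rows that matter here are:
- Visual acuity (eye-tracking): "WISC-V, symbol search"
- Visual motricity (eye-tracking): "WISC-V, symbol search, coding"
- Attention (Rocket, Connect): "WISC-V, digit span, coding, symbol search"
- Processing speed (Connect): "WISC-V, symbol search (immediate recall) coding"
- Episodic memory (O-G): "WISC-V, letter-number sequences, digit-span"

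The Participant section requires "normal hearings, normal or corrected-normal vision" for entry. The instruments to be administered are listed in Table 2 and again under Questionnaires and neuro-assessments. Each place names seven WISC-V subtests, but not the same seven.

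**The concern.** A correlation with a comparator is evidence for a domain only if the comparator measures that domain. If it measures something else, a strong correlation supports that other thing. If two domains are tested with the same stream against the same comparator, a single correlation cannot say which of them the metric reflects.

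What is at stake is which domains the study may report as validated. For the rows above, the hypothesis in Table 1 could be met in full while the metric tracked processing speed or working memory only.

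**Working it through.** **1. Layout of Table 3.** It has 17 rows and 15 domains (visuo-spatial processing takes three rows). Symbol search appears in 5 of the 17 rows: visuo-spatial processing through SES4ME, attention, processing speed, visual motricity and visual acuity. It is the only comparator in two of them, SES4ME and visual acuity.

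**2. The affected rows and their neighbours.**

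| Domain | Stream | Comparators |
|---|---|---|
| Visual acuity | eye-tracking | symbol search |
| Visual motricity | eye-tracking | symbol search, coding |
| Attention | Rocket, Connect | digit span, coding, symbol search |
| Processing speed | Connect | symbol search, coding |
| Working memory | Untangle, EEG (P3b) | letter-number sequences |
| Episodic memory | O-G | letter-number sequences, digit span |
| Auditive attention | O-METRO | digit span |

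**3. Visual acuity.** Its sole comparator also serves processing speed. Neither Table 2 nor the Questionnaires and neuro-assessments section lists an acuity test. Table 4 attaches its eye-tracking variables to attention, coordination, social interaction, information processing and stress, not to acuity. The vision criterion also narrows the range of acuity in the sample; the article gives no figure for how far.

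**4. Episodic memory.** Letter-number sequences is the only WISC-V comparator for working memory. Digit span also serves attention and auditive attention. Neither instrument list contains an episodic or delayed-recall test.

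**5. Domains sharing stream and comparator.**
- Attention and processing speed share Connect, symbol search and coding. Attention has one further comparator, digit span; processing speed has none.
- Visual motricity and visual acuity share eye-tracking and symbol search. Motricity has one further comparator, coding; acuity has none.

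**6. How far one stream reaches.** Among the five symbol-search rows, SES4ME covers 1, Rocket 1 (attention), Connect 2 and eye-tracking 2. The maximum for one stream is therefore 2, and covering all five takes at least three streams (SES4ME, Connect, eye-tracking).

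**7. Which comparators are actually administered.**

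| Subtest used in Table 3 | Table 2 | Questionnaires and neuro-assessments |
|---|---|---|
| Symbol search, coding, block design | yes | yes |
| Letter-number sequences, comprehension | yes | no |
| Digit span, vocabulary | no | yes |
| Barrage | no | no |

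Under Table 2, attention loses digit span, and its comparators become identical to those of processing speed. Under the text list, working memory has no WISC-V comparator and episodic memory has digit span only.

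**8. Illustration for the acuity row.** The article gives no expected correlation, so these inputs are assumptions: a metric driven by speed alone (loading 0.7 to 0.9), symbol search driven by speed alone (loading 0.80 to 0.85), acuity independent of both, n = 400, and strong taken as r ≥ 0.5. The expected correlation is the product of the loadings: 0.7 × 0.80 = 0.56; 0.8 × 0.80 = 0.64; 0.9 × 0.85 = 0.765. In 4,000 simulated samples per setting, r ≥ 0.5 was reached in 95%, 100% and 100%. The correlation with acuity averaged about 0 and never reached 0.5. This follows from the assumed loadings. It shows only that the hypothesis can be met without acuity being measured.

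**The case against.** Table 3 claims convergent validity only, and one test may properly serve as convergent evidence for several related constructs. The Table 1 hypothesis does not cite Table 3 or set a pass rule for each row. The Primary objective section also names sensitivity, specificity, reliability, reproducibility and predictive values. A multitrait-multimethod analysis is something a condensed article may leave to an analysis plan. These points stand: the lack of a general discriminant analysis in the article is not itself a fault.

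A reader might go further and infer that one speed-only metric would count as support for all five symbol-search domains at once. The stream column rules this out: one stream serves at most two of those rows, and three of the five rows list other comparators as well. A reader might also infer that the normative base and the transdiagnostic profiles fall with these rows. The documents do not support that either. Aims of the study works with three broad dimensions, and the Reference interval section forms profiles by unsupervised methods that are not made conditional on the Table 3 correlations.

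The objection does not rescue the two rows in which no listed instrument measures the domain. An analysis plan cannot supply a comparator that is not collected. Nor does it separate the pairs in which stream and comparator coincide.

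**Conclusion.** The point holds in a limited form. Two of 15 domains, visual acuity and episodic memory, have no relevant comparator among the listed instruments. Two pairs of domains, visual motricity with visual acuity and attention with processing speed, share both a stream and one or more comparators, so one correlation could be read as validating both members of a pair.

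This rests on Table 3's own use of symbol search for processing speed, letter-number sequences for working memory and digit span for attention. It also assumes that the two instrument lists are complete, and, for the pairs, that the same feature of the stream is used for both domains. No sample size or error rate is affected. What changes is which domains may be reported as validated.

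**What to change.** 1. Reconcile the WISC-V subtests in Table 2 and in Questionnaires and neuro-assessments with Table 3. Letter-number sequences, comprehension, digit span and vocabulary are each in only one list, and barrage is in neither. This comes first, because it decides which comparisons can be made.
2. Remove visual acuity and episodic memory from the validity claims, or label them exploratory. Removing acuity also resolves the eye-tracking pair.
3. For domains that share stream and comparators, either report them as one domain or claim them separately only if the age-adjusted correlation with a non-shared comparator exceeds that with the other domain's comparator, by a test for dependent correlations. For Connect, this means digit span against symbol search and coding. It is possible only if digit span is administered. Processing speed has no comparator of its own, so without digit span the two domains should be merged.

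The cost is revised wording in Tables 1 and 3 and one additional correlation analysis. It needs no new instrument only if the reconciled list contains the subtests concerned. The downside is that fewer domains can be claimed as separately validated.
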